### Retention

To promote participant retention and ensure complete follow-up, patients will receive email reminders to complete the follow-up questionnaire. If there is no response to the email, a reminder telephone call will be made. For participants who discontinue or deviate from the intervention protocols, any available outcome data collected up to that point will still be used in the analysis in order to maintain the integrity of the study results, as long as patient or parent consent is not withdrawn.

### Data management

Patients in the experimental group will have full control of their own data stored in the JAY smartphone app. They will decide which data they want to share, export them from the app, and upload them to a secure research server. From there, data will be stored in an encrypted data network provided and hosted by the University Hospital of Cologne.

Patients in the control group will hand their paper-based homework to their therapist, who will pass it to the project team. Again, adolescents can decide about data sharing and will have full control of their data. A designated study staff member will scan the homework and file the paper version in the respective patient file, which will be kept in a locked cabinet accessible only to study staff. The digital version will be stored in a secure network provided and hosted by the University Hospital of Cologne. Access to the project database will be restricted to authorized personnel of the research group only.

### Confidentiality

At the beginning of the study, each participant will be assigned a unique study identification number. All data collected during the study will be anonymized and can only be linked to the participant by the study staff, using the study identification number. Compliance with legal regulations for data protection will be ensured. Participating families will receive comprehensive information about their rights concerning data storage, protection, and deletion.

## Statistical methods

### Statistical methods for primary and secondary outcomes

#### Analyses of primary endpoint

The primary analysis set adheres to the intention-to-treat (ITT) principle, comprising all patients randomised with a valid baseline assessment. Additionally, per-protocol analyses will involve all patients who attend at least 50% of the planned treatment sessions and provide a valid follow-up. The primary endpoint is the overall THA score across the intervention (sessions 1–16). Subsequent analyses assess changes in phase 1 (sessions 1–8 from T1 to T2) and changes in phase 2 (sessions 9–16, between T2 and T3). A mixed model repeated measures multivariate analysis of variance will be conducted, with the between-subjects factor Group (smartphone-augmented vs. traditional), the within-subjects factor Time (T2, T3), and the interaction effect of Group × Time.

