In summary, THA is an important factor for treatment outcomes, with low THA potentially contributing to insufficient effectiveness of CBT. Indeed, studies have shown that low THA is a common phenomenon in cognitive therapy, especially in adolescents [32, 33]. For example, a study measuring homework compliance in adolescents with depression receiving CBT reported a homework completion rate of only 56%, and a decline during the therapy process was noted [34]. Non-adherence is influenced by patient, therapist, and task factors, but an empirical evaluation is impeded by various methodological difficulties [32, 35]. Nevertheless, some experience-based recommendations to improve THA can be made. For instance, homework should be meaningful, relevant to the central goals of therapy, salient to the focus of the session, agreeable to the therapist and patient, appropriate to the patient’s sociocultural context, doable, small, have a clear rationale and back-up plan, and should be practiced in session [36, 37]. It is also recommended that a time and place to complete the homework should be defined in advance [36, 37]. Accordingly, a qualitative study found that adolescent patients often perceive homework as too difficult or time-consuming and that they lack the motivation to complete it [38].

Smartphone apps may provide a way of improving mental health treatment in general and THA specifically [39–42]. Modern-day youth are growing up in an increasingly digital environment, gaining internet access at progressively younger ages [43]. Notably, around 96% of German adolescents aged 12–19 years have their own smartphone [44]. As such, mobile technology might represent a promising platform for enhancing mental health treatment [45].

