**Fig. 1 Fig1:**
[figure not shown]
Study design of the JAY trial

Following these sessions, patients will be randomly allocated to one of the two treatment arms. After randomization, a baseline phase will take place, followed by the T1 assessment. In the subsequent treatment phase, patients in both groups will receive state-of-the-art CBT. In the treatment group (CBT + JAY), homework and assessments will be conducted through the JAY app, while in the active control group (CBT), equivalent tasks will be completed on paper. Each treatment phase will consist of eight sessions with the patient and up to four sessions with a caregiver. The first treatment phase will be followed by the T2 assessment. The final main assessment (T3) will take place after the second treatment phase. Depending on the clinical significance of remaining internalizing symptoms, patients will then either continue with a third treatment phase, which will be followed by the T4 assessment, or the intervention will be stopped and they will proceed to a first follow-up assessment after 8 weeks (T4). A subsequent follow-up evaluation (T5) for all patients will be scheduled 6 months after T4.

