#### Intervention description

In the randomized control trial, each participant will receive cognitive behavioral therapy conforming to German clinical guidelines and based on international evidence-based treatment manuals (e.g., the SELBST program [81], THAZ—Social Anxiety [82], CBT for Depression in Childhood and Adolescence [83]). Participants will undergo 16 to 24 weekly therapy sessions, and up to 12 optional caregiver sessions will be provided (a maximum of four per treatment phase).

A personalized treatment plan will be created for each patient. Common elements of treatment include establishing rapport and motivation, resource activation, developing a mutual understanding of the disorder and its causes, psychoeducation, situational analysis, and setting treatment goals.

For the treatment of depressive symptoms, tailored interventions may include resource activation for low self-esteem, promoting activities for patients lacking positive experiences, problem-solving training for inadequate conflict resolution, cognitive restructuring for dysfunctional thought patterns, third-wave techniques for managing ruminative thoughts, and self-reinforcement for insufficient self-care.

Anxiety treatment may involve cognitive restructuring for dysfunctional thoughts, graduated exposure therapy combined with positive reinforcement to address avoidance behaviours, and competence training for lacking skills (such as social skills).

At the conclusion of each treatment, there will be an evaluation, relapse prevention strategies, and emotional detachment from the therapist.

The study therapies are conducted by child and adolescent therapists in training. Therapists need to be familiar with the app’s features and comfortable in incorporating the app into the therapy sessions. Otherwise, implementation of and fidelity to the intervention might be threatened. To limit this risk, therapists will receive a comprehensive introductory session to the app as well as ongoing support on how to integrate it into their therapy sessions effectively. The study staff will deliver this introductory session and offer continuous technical assistance. The supervisor will offer guidance to therapists on the effective integration of the app into therapy sessions. Additionally, a comprehensive user manual will be provided [67].

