
### Participant timeline

The participant timeline and measurement schedule for the JAY trial will include four key stages: a screening process, a baseline phase, an intervention period, and a follow-up assessment. The screening process will assess whether families meet the study’s inclusion and exclusion criteria in several steps. First, families will be contacted by telephone for a brief standardized screening. If the initial criteria are met, the patient and a caregiver will be invited for an in-depth screening and information session. Participants who agree to join the study will complete initial questionnaires and undergo three diagnostic sessions to thoroughly assess eligibility (T0). This will be followed by randomization to the experimental or control group. After this, three sessions will be conducted to introduce the patient to their therapist, focusing on building a strong patient-therapist relationship and providing psychoeducation.

The screening process will be followed by a baseline phase that does not include any sessions with the study staff or therapist. Participants will use the JAY app [67] or paper-and-pencil sheets for the purpose of self-observation.

The pre-treatment assessment (T1) will mark the end of the baseline and beginning of the treatment phase. The first part of the treatment phase will involve eight sessions of cognitive-behavioural therapy and up to four sessions with caregivers, followed by an intermediate assessment (T2). The second part of the treatment phase will likewise consist of eight patient sessions and up to four caregiver sessions. Subsequently, another main assessment (T3) will follow. Non-responders to the treatment will be identified using the Internalizing scale from the YSR/11-18R [69] and will continue to receive CBT in a third part of the treatment phase. This will then be followed by a final assessment (T4). Responders to the treatment, as indicated by a lack of significant internalizing symptoms at the main assessment (T3), will conclude their participation in the study. Eight weeks after the final therapy session, they will engage in an initial follow-up assessment (T4).

Finally, every family will complete a follow-up survey (T5) 6 months after T4.

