### Implementation

The principal investigator (PI) will supervise the randomization. Recruitment staff, who are responsible for initial evaluations, will begin this process. Next, the PI will return a digital form to the staff indicating the participant’s assigned group. The staff will then inform both the therapist and the family about the treatment details.

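### The primary model has no therapist term and the plan does not say whether each therapist treats both arms; if therapists are concentrated in one arm, the standard error is too small.

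*Protocol article*

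**What the plan says.** **Model.** Under Analyses of primary endpoint, the overall THA score is analysed "with the between-subjects factor Group (smartphone-augmented vs. traditional), the within-subjects factor Time (T2, T3), and the interaction effect of Group × Time". No therapist effect is listed. Multilevel modelling is mentioned only under Analyses of secondary endpoints, and no therapist level is named there.

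**Therapist influence.** The Background states: "Non-adherence is influenced by patient, therapist, and task factors, but an empirical evaluation is impeded by various methodological difficulties".

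**Delivery.** Intervention description states: "The study therapies are conducted by child and adolescent therapists in training". It adds: "Therapists need to be familiar with the app’s features and comfortable in incorporating the app into the therapy sessions", and warns that implementation and fidelity could otherwise suffer. The article gives no number of therapists and no caseload, and does not say whether a therapist treats patients in one arm or both.

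**Randomisation.** Sequence generation describes individual randomisation in blocks of four. No stratification by therapist is stated. The sample is 70 patients, 35 per arm.

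**Timing.** The text with Fig. 1 describes diagnostic sessions and sessions to meet the therapist, and then says: "Following these sessions, patients will be randomly allocated to one of the two treatment arms". Participant timeline puts randomisation first: "After this, three sessions will be conducted to introduce the patient to their therapist". Under Implementation, after allocation, "The staff will then inform both the therapist and the family about the treatment details".

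**The concern.** THA is the ratio of completed to requested entries multiplied by a quality score. The therapist can affect both parts. The challenge is individually assigned, the number of diary entries has only a stated minimum, and the therapist's way of setting and reviewing homework may affect how much is done and how well. Scores of patients who share a therapist may therefore be correlated.

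A model without a therapist term ignores that correlation. Whether this harms the primary comparison depends on how therapists are spread over the arms, which the article leaves open. If therapists are concentrated in one arm, differences between therapists become part of the difference between arms. The primary confidence interval is then too narrow and the false-positive rate exceeds 5%.

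**Working it through.** The plan gives no figure for therapist clustering, so there is none to reproduce. The power of 0.84 under Sample size comes from a cited study and does not bear on this point.

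**Inputs from the article:** N = 70, 35 per arm, individual randomisation in blocks of four, no therapist term.

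**Assumptions (not in the article):** number of therapists K = 10 to 20, with 35 as a many-therapist case; therapist ICC = 0.05 to 0.10; one averaged score per patient; equal caseloads; nominal two-sided alpha 0.05.

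**Layout 1: therapists nested in arm.** Mean caseload is 70/K. The design effect is DEFF = 1 + (70/K − 1) × ICC. The actual type I error of the model without a therapist term is about 2 × [1 − Φ(1.96/√DEFF)].

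| K | ICC | DEFF | √DEFF | Type I error |
|---|---|---|---|---|
| 10 | 0.05 | 1 + 6 × 0.05 = 1.30 | 1.140 | 8.6% |
| 10 | 0.10 | 1 + 6 × 0.10 = 1.60 | 1.265 | 12.1% |
| 20 | 0.05 | 1 + 2.5 × 0.05 = 1.125 | 1.061 | 6.5% |
| 20 | 0.10 | 1 + 2.5 × 0.10 = 1.25 | 1.118 | 8.0% |
| 35 | 0.05 | 1 + 1 × 0.05 = 1.05 | 1.025 | 5.6% |
| 35 | 0.10 | 1 + 1 × 0.10 = 1.10 | 1.049 | 6.2% |

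Simulation with 20,000 runs per cell agrees: 8.8% and 12.4% for K = 10, and 6.6% and 8.2% for K = 20, at ICC 0.05 and 0.10 respectively.

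**Layout 2: therapists treat both arms, patients randomised regardless of therapist.** The therapist is then an omitted prognostic factor that randomisation distributes by chance. In simulation with 6 to 20 therapists and the same ICCs, the ratio of true to model standard error was 1.00 to 1.01 and type I error was 4.7% to 5.2%. The standard error is valid, and some precision is forgone.

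**Layout 3: therapists treat both arms, arms balanced within therapist.** Therapist variance cancels from the treatment difference but remains in the model's error term. The interval is too wide by a factor of 1/√(1 − ICC): 1/√0.95 = 1.026 and 1/√0.90 = 1.054, that is 3% to 5%. Simulated type I error was 3.9% to 4.7%.

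**ICC zero.** DEFF = 1 and 1/√(1 − 0) = 1, so the stated model is correct under every layout.

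**Therapist-by-app effect.** If therapists differ in how well they integrate the app, patients of one therapist within one arm share a further component that does not cancel between arms. This can make the standard error too small even under Layout 2. Its size depends on an interaction variance that the article does not give, so no figure is put on it.

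**The case against.** A reader might infer that the standard error must be wrong in one direction or the other, whatever the layout. The documents do not support that. Layout 2 is fully compatible with individual randomisation without therapist strata, and there the standard error is essentially right. The 3% to 5% excess width of Layout 3 needs balance within therapist, which no section provides.

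A reader might also take the conflict over when the therapist is introduced as evidence of nesting. It is not: the order of those sessions does not settle whether a therapist treats one arm or both. No section ties therapists to an arm, and some text leans the other way. App familiarity is asked of therapists in general, and the wording under Implementation suggests that a therapist is already designated at allocation.

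The Background sentence should not be stretched either. It names the therapist as one of three kinds of influence and adds that empirical evaluation is difficult. A common minimum of homework, a ratio relative to what was requested, manual-based rating by five independent raters and regular supervision may all keep the therapist ICC low. The number of therapists and the ICC are assumptions, and many therapists with small caseloads would make the problem minor. All of this stands, and it makes the finding conditional.

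The last objection is that random-effect structure often sits in a statistical analysis plan. That holds only in part. The article lists the terms of the primary model and, unlike the section on missing data, does not defer that choice to such a plan. A later therapist term would be a change to what is stated.

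**Conclusion.** The point holds in conditional form. The stated primary model takes patients as independent, although the article itself names the therapist as an influence on the behaviour being measured and does not fix the therapist-by-arm layout.

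- If therapists are concentrated in one arm, type I error is inflated. It reaches about 6.5% to 12% under full nesting with 10 to 20 therapists and ICC 0.05 to 0.10, and 5.6% to 6.2% with 35 therapists.
- If therapists treat both arms and randomisation ignores the therapist, the test is valid unless therapists also differ in how the app works in their hands.
- If arms are balanced within therapist, the test is slightly conservative.
- At ICC zero nothing is wrong.

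The number of therapists, the ICC and the layouts are assumptions, because the article gives none of them. The change is worth making because the plan does not rule out the harmful layout and the protection is cheap.

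**What to change.** 1. Add a random intercept for therapist to the primary model, with small-sample degrees of freedom. If its variance is estimated at zero, the model reduces to the one now stated.
2. Add a sensitivity analysis with a therapist-by-group effect, since a random intercept alone does not cover differences between therapists in app uptake.
3. State whether each therapist treats patients in both arms, and report the number of therapists and their patients per arm.
4. Reconcile the text with Fig. 1 and Participant timeline on whether the therapist is introduced before or after randomisation.

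**Cost.** A few sentences and one variance parameter in the primary model. Therapists already complete a structured protocol after each session (Adherence section), so therapist identity should need little or no new data collection. The interval may widen if therapists prove to be nested in arm, which would then be the honest width. With 70 patients and small caseloads the therapist variance may be poorly estimated.

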#### Analyses of secondary endpoints

For the secondary outcomes, we will conduct analyses utilising either mixed models for repeated measures, employing a heterogeneous first-order autoregressive structured covariance matrix over time, or generalized estimating equation approaches with corresponding marginal means and contrast tests (multilevel modelling). Time-to-dropout distributions will be summarised using the Kaplan-Meier method and compared using the (stratified) log-rank test. Efficacy variables will be summarised by time point and treatment arm, including mean, standard deviation, percentiles (minimum, 25th, 50th, 75th, and maximum), count, and percentage. Additionally, moderation, mediation, and conditional process modelling will be performed based on regression and structural equations (interaction, simple slope analysis; direct/indirect effects, kappa squared).

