The following hypotheses will be investigated:The experimental group (CBT + JAY) will show a significantly higher overall THA score compared to the active control group (CBT) throughout the intervention phases, as assessed by quantitative aspects of therapy homework (relative ratio of completed and required entries) as well as qualitative aspects which together as a composite score constitute the primary outcome. The qualitative aspects (content fit, thoroughness, competence of behaviour/thoughts, and clinical relevance) will be evaluated by multiple independent raters using a rating system that defines the assessment criteria.The experimental group (CBT + JAY) will show higher THA compared to the active control group (CBT) as assessed using the clinician-rated Questionnaire for Therapy Adherence after each therapy session [68].The experimental group (CBT + JAY) will show a greater reduction in internalizing symptoms compared to the active control group (CBT) according to self-rating, as measured using the Internalizing Problems scale of the Youth Self-Report 11–18 (YSR/11-18R) [69, 70] as well as the self-report symptom checklists for anxiety (SCL-AD-S) and depression (SCL-DEP-S) from the “Diagnostic system for mental disorders based on ICD-10/DSM-5 for children and adolescents” (DISYPS-III) [71] and using an individual problem list.The experimental group (CBT + JAY) will show a greater reduction in internalizing symptoms compared to the active control group (CBT) according to caregiver rating, as measured using the Internalizing Problems scale of the caregiver-report Child Behaviour Checklist (CBCL/6-18R) [69, 70] as well as the caregiver-report scales for anxiety (SCL-AD-P) and depression (SCL-DEP-P) from the DISYPS-III [71].The experimental group (CBT + JAY) will show a greater reduction in internalizing symptoms compared to the active-control group (CBT) according to clinical rating, as assessed by a clinician using a structured clinical interview (ILF-INTERNAL) from the DISYPS-III [72].The experimental group (CBT + JAY) will show a stronger reduction in comorbid symptoms as measured using the scales Externalizing Problems and Total Problems of the self-report YSR/11-18R and the caregiver-report CBCL/6-18R [69, 70].Patients in the experimental group (CBT + JAY) will show a greater improvement in quality of life, sense of global self-worth, and emotion regulation strategies according to self-report compared to patients in the control group (CBT), as assessed by the Revised Questionnaire for Health-Related Quality of Life Assessment in Children (KINDL^R^) [73], by a modified German version of the Self-Perception Profile for Children called the Harter scale [74, 75], and by a modified version of the Questionnaire to Assess Children’s and Adolescents’ Emotion Regulation Strategies (FEEL-KJ) [76], respectively.Patients in the experimental group (CBT + JAY) will show greater treatment satisfaction than those in the control group (CBT), as measured by a modified version of the self-report Client Satisfaction Questionnaire (ZUF-8-M patient) [77, 78].

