#### Secondary outcomes

Secondary outcomes include:The quantity of therapy homework, as assessed by the relative ratio of completed to requested entries within the JAY app or on the paper-and-pencil sheets between the treatment sessions.Quality of the entries, as rated by a pool of clinicians based on the app entries or the homework sheets according to the rating system mentioned in the previous section.Patient-rated symptoms of anxiety and depression, assessed by the Internalizing Problems scale of the self-report YSR/11-18R [69, 70] as well as the self-report scales for anxiety (SCL-AD-S) and for depression (SCL-DEP-S) from the DISYPS-III [71]. Reliability and validity as well as sensitivity to change of the German version of the YSR/11-18R and the DISYPS-III scales have already been demonstrated in German samples [70, 71]. The Internalizing Problems scale of the YSR/11-18R will be assessed at every measurement time point and the SCL-AD-S and SCL-DEP-S will be assessed at T0 and T3.Caregiver-rated symptoms of anxiety and depression, assessed by the Internalizing Problems scale of the caregiver-report CBCL/6-18R [69, 70] as well as the caregiver-report scales for anxiety (SCL-AD-P) and for depression (SCL-DEP-P) from the DISYPS-III [71]. Reliability and validity as well as sensitivity to change of the German version of the CBCL and the DISYPS-III scales have already been demonstrated in German samples [70, 71]. The Internalizing Problems scale of the CBCL/6-18R will be assessed at every measurement time point, and the SCL-AD-P and SCL-DEP-P will be assessed at T0 and T3.Clinician-rated symptoms of anxiety and depression based on the ILF-INTERNAL from the DISYPS [72], assessed at T0 and T3.Individually defined problem behaviours were rated by the patients using an individual problem list (IPL) in every therapy session. The problem list allows for the assessment of four targeted issues, rated on a 5-point Likert scale, and of the burden of the problems, rated on a 10-point Likert scale. Individual problem lists have been shown to be reliable, valid, and sensitive to change [85].Patient- and caregiver-rated comorbid symptoms and overall behavioural and emotional problems, measured using the remaining scales Externalizing Problems and Total Problems of the self-report YSR/11-18R and the caregiver-report CBCL/6-18R [69, 70]. Reliability and validity as well as sensitivity to change of the German version of these scales have been demonstrated in German samples [70]. These outcomes will be measured at T0 and T3.Patients’ adherence during the weekly therapy sessions (e.g., engagement in tasks and activities) will be measured using the clinician-rated Adherence Questionnaire [68], which will be assessed after every therapy session. This was adapted from the AUTHARK trial [41], in which good internal consistencies were reported.Quality of life, assessed using the Revised Questionnaire for Health-Related Quality of Life Assessment in Children and Adolescents (KINDL^R^) [73], which evaluates aspects related to physical and psychological well-being, the adolescent’s self-worth, as well as friendships and family relationships. Reliability and validity as well as sensitivity to change of scale have been demonstrated in German samples [86, 87]. This outcome will be assessed at T0 and T3. Sense of global self-worth, assessed using a modified German version of the Self-Perception Profile for Children, called the Harter scale [74, 75], which evaluates perceptions of cognitive and physical competence, peer acceptance, physical appearance, and self-worth. Reliability and validity of the original scale were demonstrated in a German clinical sample [88]. This outcome will be assessed at T0 and T3. Emotion regulation strategies were assessed using a modified version of the Questionnaire to Assess Children’s and Adolescents’ Emotion Regulation Strategies (FEEL-KJ) [76], which evaluates adaptive and maladaptive strategies to regulate feelings of anxiety and sadness. Reliability and validity have been demonstrated [76]. This outcome will be assessed at T0 and T3. Retrospective mood assessments will be conducted in every week in which the patient has used the momentary assessment of the JAY app or the paper-and-pencil equivalent. All 16 momentary affective and mental states assessed during the week will be rated retrospectively for the same week on a scale from 0 to 100. Patient-rated satisfaction with the treatment, assessed using a modified version of the self-report Client Satisfaction Questionnaire (ZUF-8-M patient) [77, 78], which has been shown to be reliable, valid, and sensitive to change [89]. Satisfaction will be assessed once, at T3. Patient-rated usability of the JAY app, assessed using a German translation of the System Usability Scale (SUS), which has been shown to be reliable, usable, and valid [90]. The scale measures effectiveness, efficiency, and satisfaction of and with a system. Usability will be assessed for patients in the experimental group once, at T3. Life events in the domains of school, family, and friendships as well as illness, accidents, and losses, as measured by the Zurich Life-Event List (ZLEL), which has been shown to be reliable and valid [91]. This measure will be applied once, at the follow-up (T5) in this study.

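### For secondary outcomes measured only at T0 and T3, the plan does not provide for adjustment to the pre-randomisation T0 score; as worded, its model points to a less precise change-score comparison

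*Protocol article*

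**What the plan says.** **Model.** Under Analyses of secondary endpoints, one sentence covers all secondary outcomes. The first method it names is "mixed models for repeated measures, employing a heterogeneous first-order autoregressive structured covariance matrix over time". As an alternative it allows a GEE analysis with marginal means and contrasts. It does not say whether T0 is a response or a covariate, whether arm means at T0 are constrained, or which contrast tests the hypotheses.

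**Schedule.** Under Secondary outcomes, "the SCL-AD-S and SCL-DEP-S will be assessed at T0 and T3". The same two occasions apply to the caregiver checklists (SCL-AD-P, SCL-DEP-P), ILF-INTERNAL, the Externalizing and Total scales of the YSR and CBCL, KINDL-R, the Harter scale and FEEL-KJ. Other measures have more occasions: "The Internalizing Problems scale of the YSR/11-18R will be assessed at every measurement time point", likewise CBCL Internalizing, and individual problems are "rated by the patients using an individual problem list (IPL) in every therapy session".

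**Timing of T0.** Participant timeline: patients "undergo three diagnostic sessions to thoroughly assess eligibility (T0). This will be followed by randomization to the experimental or control group". Trial design, after the T0 questionnaires and the diagnostic and introductory sessions: "Following these sessions, patients will be randomly allocated to one of the two treatment arms". The two accounts differ on where the sessions introducing the therapist fall, but both put T0 before allocation.

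**Hypotheses.** They are worded as reduction or improvement. In hypothesis 3 the app group "will show a greater reduction in internalizing symptoms compared to the active control group (CBT) according to self-rating".

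**The concern.** Because T0 precedes randomisation, the true T0 difference between arms is zero by design. A model that estimates this difference freely and subtracts it adds noise, and it corrects in full a chance imbalance that should be corrected only in part. Adjusting for the T0 score avoids both.

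The article names no baseline adjustment anywhere. The primary model lists only Group, Time and their interaction, and baseline data are otherwise summarised descriptively. At stake is precision on the symptom, quality-of-life and emotion-regulation outcomes of a 70-patient trial, using data that the trial already collects.

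**Working it through.** **Which measures are affected**

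| Hypothesis | Measures | T0 and T3 only |
|---|---|---|
| 3 | YSR Internalizing, SCL-AD-S, SCL-DEP-S, problem list | 2 of 4 |
| 4 | CBCL Internalizing, SCL-AD-P, SCL-DEP-P | 2 of 3 |
| 5 | ILF-INTERNAL | 1 of 1 |
| 6 | YSR and CBCL Externalizing and Total | 4 of 4 |
| 7 | KINDL-R, Harter, FEEL-KJ | 3 of 3 |
| Total | | 12 of 15 |

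**What the model does with two occasions.** If T0 is a covariate, one response per patient remains and there is no covariance over time to fit. The named mixed model therefore needs T0 as a response. With free arm means and complete data, its Group × Time contrast is (mean T3 − mean T0 in one arm) minus the same in the other, which is the difference in mean change. A GEE with the same interaction gives the same contrast.

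**The plan's own figure.** The only power figure, 0.84 with 35 per group, is borrowed from another study and concerns homework adherence. The article states no standard error, correlation or power for these outcomes, so there is nothing to reproduce.

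**Inputs.** n = 35 per arm (Sample size). The T0–T3 correlation r and the SDs are assumptions.

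**Standard errors with equal SDs**, in SD units:
- change score: √(2/35) × √(2(1 − r))
- T0-adjusted: √(2/35) × √(1 − r²)
- ratio: √(2/(1 + r))

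| r | Change SE | T0-adjusted SE | Ratio |
|---|---|---|---|
| 0.3 | 0.283 | 0.228 | 1.240 |
| 0.5 | 0.239 | 0.207 | 1.155 |
| 0.7 | 0.185 | 0.171 | 1.085 |

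Generalised least squares gives the same ratios. It also shows that keeping T0 as a response with arm means constrained equal at T0 recovers the T0-adjusted SE. Multiplying the adjusted variance by 1 + 1/66, for estimating the slope with N = 70, gives ratios of 1.231, 1.146 and 1.077. A simulation (35 per arm, 4,000 runs) gave 1.23, 1.13 and 1.07. Outside this range, r = 0.1 gives 1.35 and r = 0.9 gives 1.03.

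**Unequal SDs.** With k = SD(T3)/SD(T0), the ratio is √[(1 + k² − 2rk) / (k²(1 − r²))].
- k = 0.8: 1.411 at r = 0.3, 1.262 at r = 0.7
- k = 1.25: 1.129 at r = 0.3, 1.010 at r = 0.7

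**Direction.** In units of the T0 variance, the change-score variance minus the adjusted variance is (1 + k² − 2rk) − k²(1 − r²) = (1 − rk)², which is never negative. Apart from the small cost of estimating the slope, the change score is never more precise. It is equally precise only when rk = 1, that is, when the slope of T3 on T0 is 1.

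**Power, illustration only.** For an assumed 0.5 SD effect at T3 and equal SDs, power ≈ Φ(0.5/SE − 1.96). Change versus T0-adjusted gives 0.42 vs 0.59 (r = 0.3), 0.55 vs 0.68 (r = 0.5) and 0.77 vs 0.83 (r = 0.7).

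**Chance imbalance.** The T0 arm difference has SD √(2/35) = 0.24. The change score subtracts all of it instead of r times it. At r = 0.5, a one-SD imbalance shifts the estimate by 0.5 × 0.24 = 0.12 SD relative to the adjusted one.

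**The case against.** The strongest reply is that the article does not state the criticised model. Its sentence covers every secondary outcome, including satisfaction and usability, each measured once at T3, where no covariance over time can exist. It therefore names a family of models to be adapted to each schedule. T0 as covariate with T3 as response, or T0 as a response with equal means, would be ordinary adaptations without the loss. GEE is offered as an alternative, and how a baseline score enters a model is often left to the SAP, which is not shown.

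Much of this stands. A reader might infer that the protocol prescribes a change-score analysis; it does not, and that reading is an inference from the wording and the schedule. It remains the most direct reading, because no passage provides for adjustment or for the constraint. The GEE route does not remove the problem. Group × Time is again the change contrast, and a T3 marginal-mean contrast from an unconstrained model ignores T0, with an SE 1.05, 1.15 and 1.40 times the adjusted one at r = 0.3, 0.5 and 0.7.

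A reader might also infer bias. The documents do not support that: T0 precedes allocation, so the change contrast is unbiased over randomisations, and it answers a hypothesis about reduction directly. Nor is 8% to 24% a property of this trial. The plan's heterogeneous covariance itself allows unequal SDs, and the eligibility threshold on YSR Internalizing may narrow the T0 spread on related scales, which would make the loss smaller.

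**Conclusion.** The point holds as a conditional loss of efficiency on secondary outcomes, not as an error in a stated result. For the 12 two-occasion measures, the named mixed model implies T0 as a response, and nothing in the article protects against an unadjusted change comparison. If T0 means are free and Group × Time is tested, the SE is about 8% to 24% larger than with T0 adjustment. This assumes r from 0.7 down to 0.3 and equal SDs; unequal SDs give about 1% to 13% (ratio 1.25) or 26% to 41% (ratio 0.8). The direction does not depend on these assumptions; the size does.

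A reader might extend this to all of hypotheses 3 to 7. The figures do not carry over to YSR and CBCL Internalizing or to the problem list, which have more occasions. The primary outcome is not affected.

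**What to change.** Add one sentence to Analyses of secondary endpoints, or to the SAP: for every secondary outcome with a T0 score, the arm contrast at T3 is adjusted for the T0 score of the same scale. Either of two forms will do:

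- T0 as a covariate, with a T0-by-visit term where there are several later visits.
- T0 as a response, with the two arm means constrained equal at T0. This also keeps patients who have only a T0 score in the model, which suits an intention-to-treat set defined by randomisation and a valid baseline.

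Apply the constraint at T0 only. T1 follows randomisation and a phase of app or paper self-observation, so the arms may already differ there.

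The cost is the sentence itself and one degree of freedom for the slope. The T0 scores are already collected, and the article describes recruitment as ongoing. If the SAP already specifies either form, only the article's wording needs to be aligned with it.
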